### Intervention description {11a}

Participants allocated to the intervention condition receive one of two passive back-support exoskeleton models (Model A or Model B) for 3 months, assigned randomly. This is accompanied by regular follow-up appointments and asynchronous educational materials on its use. This includes monitoring daily wearing time and frequency of use per week. Participants are instructed to wear the exoskeleton “as frequently as possible” during their daily work activities over the 3-month period. This instruction was deliberately chosen to obtain a realistic and practice-oriented representation of actual usage behavior in everyday work. Since occupational activities typically encompass a broad range of tasks (e.g., sitting, standing, lifting), participants are instructed to use the exoskeleton during at least 75% of all lifting tasks (see also primary applicability endpoint). No additional strategies to promote or enforce adherence are implemented, as justified non-use in this context provides important insights and represents a relevant aspect of ecological validity.

Daily wearing time will be assessed using a combination of self-reported wearing logs and objective sensor-based data. Participants will complete a daily wearing protocol documenting the duration and frequency of exoskeleton use during their work shifts throughout the 3-month intervention period.

In addition, the exoskeleton is equipped with an integrated motion sensor that records movement patterns indicative of exoskeleton use. Sensor-based measurements will be conducted during predefined measurement periods (selected full working weeks) rather than continuously throughout the entire intervention period. These data will be used to complement and validate self-reported wearing time and to assess the consistency and plausibility of self-reported usage patterns.

The control group will not receive an exoskeleton and will continue with their usual work. Participants in the control group will be instructed to continue their usual work practices and to refrain from using back braces or other back-support devices during the 3-month study period, unless medically indicated. Any medically necessary treatment or therapeutic measure may be initiated or continued at any time and will be documented.

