During the intervention period, several assessments will be conducted at 4-week intervals. These assessments will include questionnaires and brief interviews to identify entry barriers, acceptance, and potential barriers to implementing exoskeletons in daily work routines, as well as to assess musculoskeletal complaints, fatigue, job satisfaction, and cognitive performance. A detailed list of the constructs to be assessed and their corresponding measurement methods is provided in Table 2. The study visits for data collection are identical in both groups.

**Table 2 Tab2:** Outcomes and operationalization

Outcomes	Data collection, operationalization
*Outcome evaluation*	
• Musculoskeletal complaints	• Cornell Musculoskeletal Discomfort Questionnaire, German version (D-CMDQ) [31]
• Sick days • Medical costs (estimate)	• Number of total sick days • Number of musculoskeletal-related sick days • Medical costs per musculoskeletal-related sick day
• Physical and mental workload • Work-related exhaustion • Job satisfaction	• NASA-Raw Task Load Index, German version (NASA-RTLX) [32] • Fatigue Scale (FS) [33] • Copenhagen Psychosocial Questionnaire, German version (COPSOQ) [34] • Resting heart rate (blood pressure monitor, Boso medicus) • Resting blood pressure (blood pressure monitor, Boso medicus)
• Attention and memory performance due to low physical exhaustion (subgroup, nursing)	• Vienna Test System (WTS) [35]
*Process evaluation*	
• Applicability of the exoskeletons in real-world work settings	• Wearing time of the exoskeleton in relation to the total time of daily physical activity
• Utilization of the exoskeletons • Acceptance among participants and employers • User satisfaction • User experience and implementation barriers	• Frequency and duration of wearing per week • Technology readiness short scale (TB) [36] • Quebec User Evaluation of Satisfaction with Assistive Technology 2.0 (QUEST 2.0) [37] • Brief interview

After the intervention, the control group will also be allowed to use the exoskeleton for 3 months (waiting-control design). However, this usage period will not be included in the statistical analysis.

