##### Co-primary intervention adherence endpoint

Intervention adherence will be evaluated based on predefined compliance and retention criteria. Task-level compliance will be quantified as the proportion of lifting-task time during which the exoskeleton is worn, with a target threshold of ≥ 50%. In addition, overall wearing time in relation to daily physical activity will be assessed using an objective proxy measure derived from smartwatch-based movement recordings attached to the exoskeleton (Garmin Vivoactive 4).

Study-level adherence (retention) will be assessed as the proportion of participants who remain in the study and provide outcome data through the final 3-month assessment, with a target retention rate of ≥ 75% (i.e., dropout ≤ 25%). While dropout of up to 50% is conservatively anticipated for planning purposes, retention ≥ 75% represents the desired feasibility target.

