### Sample size {14}

This study is designed as a feasibility-oriented randomized controlled trial with a primary focus on intervention adherence under real-world working conditions. Primary feasibility outcomes include the following: (1) *task-level compliance with exoskeleton use* (worn for at least 50% of the time during lifting tasks) and (2)* study-level adherence* (defined as at least 75% retention through the 3-month assessment). The sample size is therefore primarily determined by feasibility considerations, including the availability of exoskeleton devices, recruitment capacity within cooperating companies, and the fixed project timeline.

Due to the lack of comparable prospective long-term studies on passive back-support exoskeletons in occupational settings, a formal a priori sample size calculation based on expected effect sizes for musculoskeletal outcomes was not feasible. Consequently, the study is not powered to provide confirmatory evidence regarding effectiveness-related outcomes.

Participants will be randomized using a 2:1 allocation ratio (intervention to control). The recruitment target is defined in terms of evaluable participants: 80 complete datasets in the intervention group and 40 complete datasets in the control group (total *n* = 120 complete datasets). A complete dataset is defined as outcome data available at baseline, at two intermediate follow-up assessments after 1 and 2 months, and at the final assessment after 3 months.

Given the real-world occupational setting and the multi-visit follow-up schedule, substantial attrition is anticipated. Assuming a conservative dropout rate of up to 50%, achieving 120 complete datasets may require randomizing up to approximately *N* = 240 participants (≈160 intervention, ≈80 control). Recruitment will therefore continue until these complete-dataset targets are reached, or until a maximum of *N* = 240 participants have been randomized, whichever occurs first, subject to feasibility constraints (e.g., device availability, company participation, and project timeline). The recruitment stopping rule is based on follow-up completeness and feasibility considerations and is not linked to interim effectiveness results.

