## Statistical methods

### Statistical methods for primary and secondary outcomes {20a}

Data will be analyzed using IBM SPSS Statistics (Version 29; IBM, Armonk, New York, USA). For the primary effectiveness analysis, both exoskeleton arms (Exo1 and Exo2) will be pooled into a single intervention group and compared to the control group. Exploratory analyses will additionally compare the three randomized arms separately. The primary analysis will follow an intention-to-treat (ITT) approach, meaning that all randomized participants will be analyzed in the groups to which they were initially assigned. Data from participants with missing information will be analyzed under the "missing at random" assumption. Per-protocol analyses will include only those participants in the intervention group who wore the exoskeleton at least 75% of the days each week when lifting tasks are performed. These analyses will be conducted as sensitivity analyses to assess the robustness of effectiveness-related estimates with respect to intervention adherence and wearing behavior. 

The primary applicability endpoint will be assessed descriptively. To evaluate the metric endpoints, mixed-effects models with a repeated measures structure will be estimated using restricted maximum likelihood. In this model, the measured values collected during all study visits will be considered the dependent variable. We will include treatment group (exoskeleton vs. control) and categorical time as fixed effects. Interactions between the group and time (categorical) will also be modeled. For random effects, we will include an intercept for each subject. Within the mixed models, we will estimate 95% confidence intervals (CIs) and *p*-values for contrasts between groups for the 3-month period. For sensitivity analyses, only patients with complete paired baseline and 3-month follow-up data will be included, ensuring a time difference within groups is analyzed using a paired *t*-test for dependent samples.

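### The 75%-of-tasks wearing instruction cites an endpoint set at 50% of lifting time, and the per-protocol set uses a third unit and filters only the exoskeleton arm, so it cannot serve as a robustness check

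*Protocol article*

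**What the plan says.** The Protocol article describes wearing in four places.

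- **Intervention description {11a}, instruction.** Participants are asked to wear the device as often as they can "during their daily work activities over the 3-month period". A threshold follows: "participants are instructed to use the exoskeleton during at least 75% of all lifting tasks (see also primary applicability endpoint". The unit is lifting tasks.
- **Co-primary intervention adherence endpoint.** "Task-level compliance will be quantified as the proportion of lifting-task time during which the exoskeleton is worn, with a target threshold of" 50% or more. Sample size {14} repeats it as "worn for at least 50% of the time during lifting tasks". The unit is time.
- **Table 2, applicability row.** "Wearing time of the exoskeleton in relation to the total time of daily physical activity". The denominator is all daily physical activity, and no threshold is given.
- **Statistical methods {20a}, per-protocol set.** It includes "only those participants in the intervention group who wore the exoskeleton at least 75% of the days each week when lifting tasks are performed". The unit is days, counted week by week.

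The same statistical section makes the per-protocol analysis a sensitivity analysis of how robust the effectiveness estimates are to adherence and wearing behaviour. It states no per-protocol condition for controls, although Intervention description {11a} tells them to "refrain from using back braces or other back-support devices during the 3-month study period, unless medically indicated". The primary effectiveness analysis is intention-to-treat, and the adherence endpoint is reported descriptively.

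**The concern.** There are two problems.

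First, the instruction directs the reader to an endpoint that does not contain the rule it is said to contain. A reader cannot tell whether the co-primary threshold is 75% of tasks or 50% of time. The set called adherent in the effectiveness analysis is then built on neither. Workers counted as compliant in the feasibility result can be missing from the per-protocol set, and non-compliant workers can be in it.

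Second, the per-protocol filter acts on behaviour after randomisation and in one arm only. The exoskeleton side keeps the workers who went on wearing the device, while the control side keeps everyone. Randomisation no longer protects that comparison. The plan nevertheless presents it as a test of robustness, so a per-protocol estimate close to the intention-to-treat estimate would be read as reassurance it cannot give.

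**Working it through.** **The plan's own arithmetic.** The only calculated figure is the recruitment ceiling in Sample size {14}: 120 / (1 − 0.50) = 240, that is 80 / 0.50 = 160 and 40 / 0.50 = 80. It reproduces, and this point does not change it.

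**Do the criteria agree?** Each usage pattern below is scored as the rules are worded. The patterns are assumptions: five lifting days a week and, except in the last row, 20 lifts and 60 minutes of lifting a day. Lifts are of equal length except in the fourth row. A day counts as worn if the device was used at all, because no daily minimum is stated.

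| Pattern | Tasks (≥75%) | Time (≥50%) | Days (≥75%) |
|---|---|---|---|
| 2 of 20 lifts, every day | 10% fail | 10% fail | 5/5 = 100% pass |
| All lifts on 3 of 5 days | 60% fail | 60% pass | 3/5 = 60% fail |
| 12 of 20 lifts, every day | 60% fail | 60% pass | 100% pass |
| 16 lifts of 1 min worn, 4 lifts of 11 min not, every day | 16/20 = 80% pass | 16/60 = 27% fail | 100% pass |
| 16 of 20 lifts, every day | 80% pass | 80% pass | 100% pass |
| 60 lifts on each of 2 days, all worn; 10 on each of 3 days, none worn | 120/150 = 80% pass | 80% pass | 2/5 = 40% fail |

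Passing one criterion does not guarantee passing another. The second row needs only equal lifting time per day. It shows a worker who meets the co-primary criterion and is excluded from the per-protocol set. The first row is the reverse case and does need the any-use reading of a worn day. The same holds for 15 of 120 lifting minutes on every day: 15/120 = 12.5% of time but 100% of days.

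**What does the one-sided filter do?** Let e be the share of the exoskeleton arm that is excluded, and δ the difference in untreated course between wearers and non-wearers, in SD units. By randomisation, controls have on average the untreated course of the whole exoskeleton arm, (1 − e) × wearers + e × non-wearers. Wearers minus controls is therefore e × δ even if the device does nothing. The documents give neither e nor δ. With e = 0.5 and δ between −0.3 and +0.3 (both assumed), the bias runs from 0.5 × (−0.3) = −0.15 SD to 0.5 × 0.3 = +0.15 SD. Its sign is that of δ.

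**The case against.** The strongest reply is that the figures do different jobs: an instruction, a feasibility target and an analysis-set filter. An instruction stricter than a success threshold is no error, and a worker wearing the device for 80% of lifts every day satisfies all three. This stands, and the criteria should not be called mutually exclusive. It does not explain the cross-reference, which presents the 75% task rule as belonging to an endpoint set at 50% of time.

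The per-protocol analysis is only a sensitivity analysis in an estimation-focused trial, and no section promises to link the two co-primary results through it. This also stands and limits the harm. A wearing filter cannot be applied to people without a device, but controls do have a conduct rule that could be used. An analysis plan might define how much wear makes a day count. That would affect the first-row example but not the second, nor the choice of unit.

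A reader might infer three stronger things that the documents do not support.

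- **That the filter flatters the device.** The Discussion links low adherence to discomfort, workflow interference and lack of perceived benefit. That says nothing about untreated prognosis, and workers with more complaints might wear the device more.
- **That the weekly rule will empty the set.** If every week of 12 must pass, and each worker has the same independent 95% chance per week, 0.95^12 = 54% remain; at 90%, 0.90^12 = 28%. Wearing habits probably persist within a worker. With full persistence 95% and 90% remain, so the ranges are 54–95% and 28–90%.
- **That the co-primary effectiveness result is compromised.** It is intention-to-treat and does not use the per-protocol set.

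**Conclusion.** The point holds in a limited form. The wearing instruction and the co-primary adherence endpoint are tied together by a cross-reference that is wrong in threshold and unit. Table 2 adds a further denominator, and the per-protocol set is built on a third unit. The mismatch can misclassify workers in both directions: one direction follows from the wording with equal lifting days, while the other also assumes that any use makes a day count.

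The per-protocol contrast compares a self-selected subset with unselected controls, so its agreement with the intention-to-treat estimate is not evidence of robustness. Neither the size nor the direction of the bias can be derived from the documents. The ±0.15 SD range is illustrative and rests entirely on the assumed values.

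The damage falls on one sensitivity analysis and on how adherence is reported and read. The intention-to-treat estimate and the recruitment figures do not change. It should be corrected, but it does not threaten the trial.

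**What to change.** 1. Reconcile Intervention description {11a}, Table 2, the co-primary adherence endpoint with Sample size {14}, and the per-protocol rule in Statistical methods {20a}, and correct the cross-reference. Which wearing instruction participants should receive is for the investigators; this review does not choose one.
2. Define the per-protocol set on the co-primary compliance metric and cut-off, summarised over the whole intervention period from the wearing logs. The endpoint already needs a lifting-time denominator, so this asks for no new quantity. If that denominator is not available for the whole period, keep the day-based rule, justify it, and state what makes a day count as worn.
3. Apply the existing rule on other back-support devices, with its medical exception, to controls in the per-protocol set.
4. Label the per-protocol result descriptive and non-randomised, and drop the claim that it tests robustness.

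An instrumental-variable analysis with arm as instrument is optional. If used, it should treat wearing as a continuous dose and state the exclusion restriction. A binary 50% cut-off threatens that restriction, because wear below the cut-off may still have an effect. Suppose half the arm is adherent and the rest gain half the benefit (assumed values). Intention-to-treat is then 0.5 × 1 + 0.5 × 0.5 = 0.75 of the full effect, and dividing by 0.5 gives 1.5, a 50% overstatement. The open-label, self-reported outcome threatens the restriction as well.

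The cost is slight rewording in a few places and a per-protocol result that carries less weight. No sample size or data collection change follows if the lifting-time denominator is already recorded for the endpoint.

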### Criteria for discontinuing or modifying allocated interventions {11b}

No modifications are planned for the allocated intervention. The aim of the study is to assess the practical applicability of the exoskeleton under real-world working conditions. Should participants wish to discontinue the intervention—for example, due to discomfort or other subjective complaints—such discontinuations will be considered important study outcomes. These decisions provide valuable insights into the acceptability and user experience of the exoskeleton.

### Strategies to improve adherence to interventions {11c}

To support compliance and adherence, research staff will be available on request throughout the intervention period to assist participants, answer questions, and verify correct exoskeleton use. Upon enrollment, participants receive standardized information and training on the purpose of the study, correct use of the exoskeleton, and study procedures.

No additional strategies to actively promote or enforce adherence (e.g., reminders, incentives, real-time feedback on wearing time, or communication of usage data to workplaces or supervisors) are implemented. This decision was made deliberately to avoid influencing natural usage behavior and to preserve ecological validity by capturing realistic patterns of exoskeleton use under routine working conditions.

### Relevant concomitant care permitted or prohibited during the trial {11d}

N/A. No specific concomitant care is prohibited during the trial.

### Provisions for post-trial care {30}

As the intervention involves the use of a passive back-support exoskeleton with minimal risk, no specific post-trial care is planned. Participants will be informed about the study results upon request. After completion of the study, all participants will return the exoskeletons to the study team; no post-trial access to the device is provided.

### Outcomes {12}

Primary and secondary outcomes are listed below. To ensure confidentiality of personal information, participants will be assigned numerical study codes. Table 3 summarizes all measurement time points.

**Table 3 Tab3:** Schedule of enrollment, interventions, and assessments

		**Study period**				
	**Screening**	**Baseline**	**Call**	**1 month**	**2 months**	**Final examination**
**Examination**	**−t**_**1**_	**t**_**0**_		**t**_**1**_	**t**_**2**_	**t**_**3**_
**Time (weeks)**	−2	0	1	4	8	12
**Socio-demographic and clinical data**						
Inclusion and exclusion criteria	**x**					
Written consent		**x**				
Randomization		**x**				
Demographic data and medical history		**x**				
Exoskeleton training		**x**	**x**			
**Evaluation of effects**						
Musculoskeletal complaints (D-CMDQ)		**x**				**x**
Number of sick days (total, musculoskeletal)		**x**		**x**	**x**	**x**
Work armouring (NASA-RTLX)		**x**		**x**	**x**	**x**
Fatigue (FS)		**x**		**x**	**x**	**x**
Work-related psychosocial stress (COPSOQ)		**x**				
Job satisfaction (Item B11.7 COPSOQ)		**x**		**x**	**x**	**x**
Cognitive performance (Vienna Test System)^a^		**x**				
Resting heart rate^b^		**x**				**x**
Resting blood pressure^b^		**x**				**x**
**Evaluation of applicability**						
Wearing frequency (per week)				**x**	**x**	**x**
Acceptance (TB)		**x**				
Usability (QUEST 2.0)				**x**	**x**	**x**
Implementation barriers (free text, optional)		**x**		**x**	**x**	**x**
Barriers to implementation (interview)				**x**		**x**
**Intervention group (IG)/control group (CG)**						
Use of exoskeletons (IG)						
Normal workflow (CG)						

*Abbreviations*: *D-CMDQ* Cornell Musculoskeletal Discomfort Questionnaire (German), *NASA-RTLX* NASA-Raw Task Load Index, *FS* Fatigue Scale, *COPSOQ* Copenhagen Psychosocial Questionnaire, *TB *Brief Technology Readiness Scale, *QUEST 2.0* Quebec User Evaluation of Satisfaction with Assistive Technology 2.0, *IG* intervention group, *CG* control group

^a^Cognitive performance: pre-post-measurement during one shift *with* and one shift *without* exoskeleton

^b^heart rate and blood pressure: at least 2 measurements per day (morning, evening) for 3 days

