A crossover design was deliberately not chosen due to important methodological and practical limitations in this occupational setting. Although laboratory studies suggest that exoskeleton use can acutely influence movement patterns, muscle activation, and perceived workload, evidence regarding the persistence and reversibility of such changes under real-world working conditions is currently limited. In particular, no evidence-based washout period can be defined. Consequently, potential carryover effects cannot be reliably excluded. To minimize the risk of residual behavioral or motor adaptations compromising internal validity, a parallel-group design was considered the more appropriate and methodologically robust approach to address the research question.

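### Cognitive performance is scheduled inconsistently, and the group-by-time model stated for metric endpoints cannot estimate a device effect from the data that Table 3 and its footnote describe

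*Protocol article*

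**What the plan says.** Objectives {7} lists possible effects on cognitive performance among the secondary objectives. Table 2 restricts the test to a nursing subgroup and names no randomised arm.

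The protocol article describes the timing in three ways:

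- The abstract has outcomes assessed at baseline, every 4 weeks during the intervention and directly after it, and names cognitive performance among them. Intervention description {11a} says that the 4-weekly questionnaires and interviews serve "as well as to assess musculoskeletal complaints, fatigue, job satisfaction, and cognitive performance".
- In Table 3 the row "Cognitive performance (Vienna Test System)^a" carries one mark, at t0. There is none at t1, t2 or t3.
- Footnote a describes the measurement as "pre-post-measurement during one shift" with the exoskeleton and one shift without it.

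For the two groups, Intervention description {11a} states "The study visits for data collection are identical in both groups", and Participant timeline {13} repeats this. The same {11a} section states "The control group will not receive an exoskeleton and will continue with their usual work".

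Statistical methods {20a} gives one model for metric endpoints: a mixed model fitted by restricted maximum likelihood to the values from all study visits. It has group (exoskeleton or control), categorical time and their interaction as fixed effects, a random intercept per subject, and group contrasts for the 3-month period. No other model is given for cognitive performance.

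**The concern.** Schedule, footnote and model describe three different measurements. The text implies a repeated outcome over four visits. Table 3 shows a single occasion. The footnote describes a with/without comparison inside the same person. The {20a} model suits only the first of these.

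At stake is whether a stated secondary objective can be analysed as written, and whether site staff can tell who is tested, when and in which condition. Recruitment began in January 2026 (Trial status), so the question is a practical one. There is also a point of interpretation. If the mark at t0 is literal, the shift with the device falls around the first training, whereas Trial design {8} justifies the 3-month period by adaptation that may take several weeks. A baseline result would then describe an acute effect, not a medium-term one.

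**Working it through.** **The plan's own figure.** No planning figure exists for this outcome. The only one that can be reproduced is the cap on randomisation: 120/(1 − 0.5) = 240, split as 80/0.5 = 160 and 40/0.5 = 80. It agrees with Sample size {14} and does not bear on this point.

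**Can the stated model estimate the effect?** Inputs: the visits marked in Table 3 and the fixed effects in {20a}. With four visits (t0 to t3) the columns are

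1 intercept + 1 group + 3 time indicators + 3 group-by-time terms = 8.

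Two contrasts matter at month 3:

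- difference in change from baseline = the group × t3 coefficient;
- group difference at t3 = the group coefficient + the group × t3 coefficient.

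A contrast is estimable if adding it as a row does not raise the rank of the design matrix.

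| Visits with data | Rank of 8 | Group × t3 | Group difference at t3 |
|---|---|---|---|
| t0 only (cognitive test in Table 3) | 2 | not estimable | not estimable |
| t0 only, all four footnote values entered | 2 | not estimable | not estimable |
| t0 and t3 (the D-CMDQ pattern) | 4 | estimable | estimable |
| t0 to t3 | 8 | estimable | estimable |

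With t0 alone, only the intercept and the group term are identified, that is, a group difference at baseline. The four values per person (2 shifts × 2 measurements) do not help, because the model has no term for device condition or for before and after the shift.

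**What the footnote data can estimate.** A model with intercept, device, post-shift and device × post-shift has 4 columns and rank 4. The device × post-shift term is estimable. It is a within-person contrast and not the one stated in {20a}.

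**Who works the shift with the device?** There are two readings:

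- The identical visits include footnote a. Controls then work one shift with the exoskeleton, against the statement in {11a} that they receive none.
- They do not include it. The visits are then not identical for this outcome, and the footnote's with/without comparison has no between-group counterpart.

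Either way, one sentence needs correcting.

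**Practice.** Number the sittings 1 and 2 (first shift) and 3 and 4 (second shift), and let g12 and g34 be the practice gains within each shift. A gain that raises sittings 3 and 4 equally cancels in the pre-post change of the second shift. What remains, for the change with the device minus the change without it, is

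- no-device shift first: g34 − g12;
- device shift first: g12 − g34.

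Under balanced random order the mean is ½(g34 − g12) + ½(g12 − g34) = 0. Under one fixed order it is zero only if g34 = g12.

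**The case against.** The strongest reply is that this is an exploratory, nursing-only outcome in a trial that disclaims confirmatory testing, and that one mark in Table 3 need not mean one moment. Footnote b attaches three days of readings to a single mark, and two shifts cannot be one moment anyway. A full analysis plan may name a suitable model. The exploratory status limits the weight of the point. A broader reading of the mark does not rescue the stated model, since the four values carry no later study visit. A separate plan could supply the model, but it would not remove the conflict between the published text, Table 3 and {20a}.

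Several stronger readings are tempting and are not supported:

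- A reader might infer that the control arm will be exposed to the device. The document never says so, and {11a} says that controls receive none. Exposure follows only if the identical visits are taken to include footnote a.
- A reader might see a contradiction with the statement "A crossover design was deliberately not chosen due to important methodological and practical limitations in this occupational setting". That passage defends the parallel design of the whole trial. A two-shift comparison in a subgroup is a different matter. Carry-over is a fair caution there, not a self-contradiction.
- A reader might count the absence of a shift order as an error. The article is silent on order, and a full protocol may fix it.
- A reader might expect a practice gain between shifts to appear in full as a device effect. On pre-post change within a shift, a constant gain cancels; only unequal gains within shifts remain.
- A reader might conclude that the objective cannot be answered at all. The footnote's data support a within-person estimate.

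**Conclusion.** The point holds as an inconsistency with a definite consequence: the analysis stated for metric endpoints cannot deliver a device effect on cognitive performance. With the Table 3 schedule, 2 of 8 fixed-effect terms are identified and neither month-3 contrast is estimable. The co-primary endpoints are untouched. The correction should be made because the outcome serves a stated objective and the repair is cheap.

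The conclusion assumes that the Table 3 row was reproduced correctly, which is likely because neighbouring rows carry marks at t1 to t3, and that {20a} is meant to cover this outcome, since no other model is given for it. It needs no assumption about effect size, variance or practice gain. Exposure of controls remains conditional on how the statement about identical visits is read.

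**What to change.** - Reconcile the abstract, {11a}, Participant timeline {13}, Table 3 with footnote a, and {20a} on who takes the cognitive test, when, and in which condition. Exempt this outcome from the statement about identical visits if it is run in one arm.
- Name it a within-person substudy in nurses, not a randomised group comparison.
- State its own model: pre-post change per shift as the outcome, fixed effects for condition (with or without the device) and shift order (first or second), and a random person effect.
- Allocate shift order at random in balanced fashion, because unequal practice gains across sittings would otherwise be confounded with the device.
- Limit it to intervention-arm nurses. Testing controls in the waitlist period is not open as things stand, since Trial design {8} and {11a} exclude that period from the analysis.

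Costs: mostly wording, and no sittings beyond the four that footnote a implies. Fewer participants contribute; under the 80:40 target, leaving out controls removes about 40/120 = one third of nurses if the ratio holds in that sector. The number of nurses is not stated. One assigned shift without the device must be reconciled with the wearing instruction in {11a}. Possible carry-over between the shifts should be stated as a limitation.
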